### Follow-up

Data collection and total follow-up will be six months.

### Data management and statistical analysis

Feasibility: a future definitive RCT to study the effectiveness of the MiLES intervention will be considered feasible when all of following criteria are met:

1. Criterion for appropriateness of inclusion criteria and for recruitment: ≥ 70% of the individuals who gave permission for telephone contact are willing to participate in the study;
2. Criterion for appropriateness of protocol: ≤ 20% do not want to participate due to the randomization procedure or are lost to follow-up due to randomization in the control group;
3. Criterion for appropriateness protocol: ≤ 20% of the participants are not willing to inform their employer about the online toolbox after randomization into the intervention group;
4. Criterion for retention rate: ≤ 20% of the participants are lost to follow-up; and,
5. Criterion for reach: the sample size number of 90 participants is included within the recruitment period of six months, starting when the first individual is invited by their treating physician.

Effect measures: equal distribution between the intervention and control group at baseline will be determined using chi-square tests for categorical variables and Student’s t-tests (normally distributed variables) or Mann-Whitney U tests (not normally distributed variables) for continuous variables. When no statistically significant unequal distributions will be found at baseline, the relative risk (RR) will be determined for RTW at T1 and T2, and a longitudinal multilevel analysis will be performed with the group classification as an independent variable and I-RTW_CS scores at the different time point (T0, T1 and T2) as dependent variables.

In the event of significant imbalance of a prognostic factor for the primary effect measure at baseline (9, 10), this factor will be used as a covariate for the analysis of that effect measure. In that case, a logistic regression analysis will be used to examine differences between the intervention and the control group with regard to RTW. For the subgroup of participants who did return to work, a longitudinal multilevel analysis will be performed to examine the difference between both groups with regard to I-RTW_CS scores. We hypothesised that participants in the intervention group 1) returned to work more often and 2) with a higher I-RTW_CS score, compared to the control group.

A longitudinal multilevel analysis will be performed for the secondary outcome effect measures. The group classification will be set as independent variable and the QWLQ-CS score as dependent variable. For unwanted work changes (i.e. at least one unwanted work change), the RR will be determined at T1 and T2.

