Time points data collection: baseline, before randomisation [T0], after 3 months of follow up [T1] and after six months of follow up [T2].

Randomization: using the electronic data-capture system Castor; allocation ratio will be set at 2:1 (intervention vs. control group); controlled the participant’s RTW status; neither the participant nor the research team will be blinded for the randomization.

Graphic outline: see figure 1.

[figure not shown]

**Figure 1.** Graphic outline of the study design and procedures using a flow diagram.

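### Baseline significance tests choose between a crude relative risk and a covariate-adjusted logistic model for RTW, so neither the adjustment nor the effect measure is fixed in advance

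*Protocol*

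**What the plan says.** The rule stands in the Protocol, section Data management and statistical analysis. It begins with significance tests of baseline balance: "equal distribution between the intervention and control group at baseline will be determined using chi-square tests for categorical variables", with t or Mann-Whitney tests for continuous variables. Two branches follow.

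- Nothing significant: "When no statistically significant unequal distributions will be found at baseline, the relative risk (RR) will be determined for RTW at T1 and T2". No covariate is mentioned.
- A prognostic factor significant: "In the event of significant imbalance of a prognostic factor for the primary effect measure at baseline", then "this factor will be used as a covariate for the analysis of that effect measure", and for RTW "In that case, a logistic regression analysis will be used to examine differences between the intervention and the control group with regard to RTW".

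Two cited reviews are given as the source of prognostic factors, but no factor is named. Nothing says how a logistic result would be expressed or converted to a relative risk (RR).

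The Methodology section adds that the "allocation ratio will be set at 2:1 (intervention vs. control group" and that randomisation is controlled for the participant's RTW status. That status does not reappear in the RTW analysis. The Project summary and the Study goals and objectives both judge effectiveness by significant superiority on two components, of which RTW is one.

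**The concern.** Under randomisation, a significant baseline difference is a chance event. Its p-value says nothing about whether the factor affects RTW, and that is what decides whether adjustment is useful. A strongly prognostic factor with a sizeable but non-significant imbalance is ignored, while a weak one that happens to cross the threshold is adjusted for.

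The gate also changes the quantity estimated. A crude RR is a marginal measure. Logistic regression naturally gives a conditional odds ratio (OR). The two are not interchangeable when RTW is common.

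The branches are not exhaustive either. If only a non-prognostic variable differs significantly, the condition for the first branch fails and the condition for the second is not met.

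At stake are the interpretability of the preliminary effect estimate and the effectiveness statement that rests on it.

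**Working it through.** The protocol gives no alpha, RTW rate, number of baseline variables or derivation of its sample size, so there is no stated figure to reproduce. What follows sizes the problem under stated assumptions.

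**Inputs.** Total 90 ("the sample size number of 90 participants is included within the recruitment period of six months") at 2:1, hence 60 versus 30. Assumed: two-sided 5% baseline tests, independent of each other.

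**1. Imbalance that escapes adjustment.**
- Continuous factor: the smallest significant difference is t(0.975, 88) × √(1/60 + 1/30) = 1.987 × 0.2236 = 0.44 SD.
- Binary factor, 30/60 (50%) versus 21/30 (70%): pooled proportion 51/90 = 0.567; SE = √(0.567 × 0.433 × 0.05) = 0.111; z = 0.20/0.111 = 1.80; p = 0.07, not flagged. With the direction reversed (42/60 versus 15/30) it is also not flagged; 43/60 would be the first significant count.

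**2. Chance of switching model.** The logistic branch needs a significant *prognostic* factor. With k such factors tested, the chance is 1 − 0.95^k:
- k = 1: 5%
- k = 3: 14%
- k = 5: 23%

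The protocol does not give k.

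**3. Difference in scale (assumed RTW rates).** For 60% versus 75%, RR = 0.75/0.60 = 1.25 and OR = (0.75/0.25)/(0.60/0.40) = 2.0. For 50% versus 70%, RR = 1.40 and OR = 2.33. These are unadjusted ORs, shown only to illustrate the gap between the scales.

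**4. Conditional bias.** Simulation of 40,000 trials with no true effect, 60 versus 30, RTW about 58%, one covariate with log-odds slope 0.8 or 1.2 per SD:
- The unadjusted comparison rejects in 5.1% to 5.2% of all trials.
- A non-significant imbalance above 0.3 SD in either direction occurs in about 13% of trials; among these the unadjusted test rejects in 7.7% to 8.7%.
- Where that imbalance lies in the direction that favours the intervention (about 6.4% of trials), the geometric mean RR is 1.12 to 1.17 instead of 1.00.

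**5. Lost precision.** Power with a true log-odds effect of 1.1, one covariate, 3,000 trials per row:

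| Covariate OR per SD | Planned rule | Always adjusted | Gain (points) |
|---|---|---|---|
| 1.22 | 65.6% | 65.4% | −0.2 |
| 1.49 | 62.8% | 63.7% | 0.9 |
| 2.01 | 59.5% | 61.5% | 2.0 |
| 3.0 | 50.5% | 57.4% | 6.9 |
| 4.95 | 40.5% | 49.9% | 9.4 |

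Each power figure carries a Monte Carlo standard error of at most √(0.25/3000) = 0.9 points. Independent repeats of the last two rows put the gain between about 5 and 11 points.

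**The case against.** The strongest defence is that this is a feasibility trial. Effectiveness is a secondary aim, described as preliminary in the Rationale & background information, and none of the five feasibility criteria uses the RTW estimate. The rule cannot change the primary conclusion. This stands, and it lowers the weight of the point.

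Several stronger readings are tempting but not supported.

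- *The model is more likely than not to switch.* With 10 or 15 independent baseline variables, the chance that at least one is significant is 40% or 54%. But that counts any variable, whereas the logistic branch requires a prognostic one. The larger figures describe leaving the first branch, not entering the second.
- *An OR will be reported.* The protocol never says odds ratio. It follows naturally from logistic regression, but an RR can be derived from that model. What the text supports is that the effect measure in that branch is left open.
- *Type I error is inflated.* Over all randomisations the unadjusted comparison holds its level. The distortion is conditional on the imbalance that occurred.
- *Power suffers substantially.* That needs a covariate OR of 3 to 5 per SD, for which the protocol gives no support. Baseline RTW status, an obvious candidate for so strong a predictor, is already controlled in the randomisation and so is unlikely to be badly imbalanced. Up to an OR of 2 the loss is about 0 to 2 points.
- *The definitive trial's sample size is spoiled.* Crude RTW proportions by arm will be available under either branch, and RR and OR can be converted given the control risk.

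Deferral to a statistical analysis plan is no answer, because the protocol itself writes the data-dependent rule.

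**Conclusion.** The point holds and should be fixed, but it is not critical. The protocol lets baseline p-values decide whether a prognostic factor is adjusted for and which model is used for RTW. It leaves one outcome of the baseline tests without an analysis and omits baseline RTW status although randomisation is controlled for it. That omission matters because participants may be only partially sick-listed at entry, so some may already be working at T0.

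The harm is threefold: bias conditional on unflagged imbalance, a loss of precision that is negligible for weak covariates and about 5 to 11 power points for very strong ones, and an effect measure not fixed ahead of a declared effectiveness decision.

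The sizes rest on a 60/30 split, 5% independent baseline tests, and covariate strengths and RTW rates that are assumed, not taken from the protocol.

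**What to change.** In Data management and statistical analysis:

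- Delete the baseline significance tests and both branches. Describe baseline data by arm without tests.
- Name one effect measure for RTW at both T1 and T2: an adjusted RR, from modified Poisson regression with robust standard errors or from logistic regression standardised to a marginal RR.
- Always adjust for T0 RTW status and a small set of prognostic factors already collected at T0, named before the data are seen. Naming them early matters all the more because "neither the participant nor the research team will be blinded for the randomization".
- Fix the covariates of the I-RTW_CS model in advance in the same way.

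Both planned time points should stay; nothing in this point justifies dropping T1.

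The cost is wording, with no new data if the factors are already measured at T0. The downside is that a few covariates must be chosen now, and a weak one will bring little gain. With about 30 controls, the list should be short.

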### Methodology

Interventions: the intervention consists of an online toolbox targeting the participant’s employer. With ‘employer’ we refer to the person who is, from his/her role as (direct) supervisor, human resource manager or case-manager, in direct contact with the participant and from there responsible for guiding the participant at work. The online toolbox is an open-assess website containing to-the-point information, videos and checklists to support employers during the RTW process of an employee diagnosed with cancer.

Intervention group: participants randomised in the intervention group will be asked to inform their employer about the online toolbox, either by email or letter. Employers will be asked to use the online toolbox throughout the RTW process of the participant.

Control group: participants randomised to the control group will not inform their employer about the online toolbox for a period of six months.

Primary outcome measure: feasibility of a future definitive RCT on the effectiveness of the MiLES intervention (in terms of reach, appropriateness of inclusion criteria, recruitment rate and appropriateness of the study protocol).

Primary effect measure: the primary effect measure of the intervention is the combined effect measure successful RTW. This effect measure is a combination of RTW (having performed work activities in own work or in replacement work during the past four weeks) and a subgroup analyses for the ones that did return to work: degrees of successfulness of RTW (a new weighted, on individual level, outcome measure) (7). The degree of successfulness of RTW contains seven items, which were found to constitute successful RTW most importantly, according to employees diagnosed with cancer: ‘enjoyment in work’, ‘work without sacrificing health’, ‘open communication with employer’, ‘perceived confidence from employer without assumptions about workability’, ‘feeling welcome at work’, ‘good work-life balance’ and ‘joint satisfaction about the work situation (employer and employee)’. Each participant rates each items on its perceived importance and on its success. The combination of the items’ relative perceived importance and the items’ success determines the degrees of successfulness of RTW.

Secondary effect measures: Quality of Working life (QWLQ_CS) (8) and number of unwanted work changes (#).

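### The I-RTW_CS multilevel model counts the pre-randomisation T0 score as an outcome and names group as its only predictor, so, read as written, it dilutes the intervention effect

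*Protocol*

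**What the plan says.** In the protocol, Data management and statistical analysis, the degree of successfulness of return to work (RTW) is to be analysed by a longitudinal multilevel model "with the group classification as an independent variable and I-RTW_CS scores at the different time point (T0, T1 and T2) as dependent variables". The Methodology section gives the visits as "baseline, before randomisation [T0], after 3 months of follow up [T1] and after six months of follow up [T2", so the first of the three outcomes is recorded before allocation.

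No other model term is named. A further covariate enters only if a prognostic factor is significantly imbalanced at baseline; in that case "this factor will be used as a covariate for the analysis of that effect measure".

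The score is not meant for everyone. Methodology describes it as "a subgroup analyses for the ones that did return to work", and the Project summary admits people who are fully or partially sick-listed.

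On the question to be answered, the Project summary and Study goals and objectives first speak of greater improvement in the intervention group, and then describe the component as a significantly higher degree of success.

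For the secondary questionnaire the text is shorter: "The group classification will be set as independent variable and the QWLQ-CS score as dependent variable". No visits are listed there.

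**The concern.** Randomisation makes the expected group difference at T0 zero. If T0, T1 and T2 are all outcomes and group is the only predictor, the group coefficient is a weighted mean of three visit-specific differences, one of which cannot carry an effect of the toolbox. The baseline score, which could sharpen the comparison as a reference point, instead pulls the estimate towards zero.

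The coefficient also does not answer a question about improvement, because a difference in change from T0 needs a group-by-time contrast or an equivalent baseline adjustment. The same paragraph takes the relative risk for RTW at T1 and T2 only, so within the primary effect measure the pre-randomisation visit is an outcome for the I-RTW_CS component alone.

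At stake is the preliminary effect estimate for one of the two components of the primary effect measure. The error is one of dilution and lost power. It does not raise the false-positive rate, since with no effect all three expected differences are zero.

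**Working it through.** **Inputs from the protocol.** Outcomes at T0, T1 and T2, group as predictor, T0 before randomisation. Allocation: "allocation ratio will be set at 2:1 (intervention vs. control group". Size: "the sample size number of 90 participants is included within the recruitment period of six months", hence 60:30. No effect size, standard deviation, correlation or share of participants with a T0 score is given, so those below are assumptions. The figure of 90 comes without a derivation, and nothing here depends on it except the power illustration.

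**1. Everyone has a T0 score.** Let the effect be d at T1 and T2. With exchangeable within-person correlation (a random intercept) the three visits have equal weight:

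(0 + d + d)/3 = 0.667d, a loss of one third at any correlation.

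A simulation of 200 trials (60:30, d = 0.50 SD, correlation 0.5) gave a mean estimate of 0.327 SD for the group-only model (Monte Carlo standard error 0.013, theory 0.333). A model with a common T0 mean and a group effect only after baseline gave 0.503 SD.

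**2. Some participants have no T0 score.** Under exchangeable correlation ρ, a person with n visits has weight n/(1 + (n − 1)ρ). At ρ = 0.5 this is 3/2 = 1.5 with three visits and 2/1.5 = 1.333 with T1 and T2 only. If a share f has a T0 score and the rest have T1 and T2:

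estimate/d = [f × 1.5 × 0.667 + (1 − f) × 1.333] / [f × 1.5 + (1 − f) × 1.333]

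- f = 0.25: 1.250/1.375 = 0.909
- f = 0.50: 1.167/1.417 = 0.824
- f = 0.75: 1.083/1.458 = 0.743

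Varying ρ from 0.3 to 0.7, and letting half of those without a T0 score contribute T2 only, gives losses of 9–11%, 17–20% and 25–27%: about 10%, 18% and 26%.

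**3. Fixed time effects.** Adding visit effects without a group-by-time term leaves these losses essentially unchanged.

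**4. Other patterns, complete T0 scores.**
- Serial (AR(1)) correlation gives T0 a weight of 1/(3 − ρ): 0.370, 0.400 and 0.435 at ρ = 0.3, 0.5 and 0.7, so losses of 37%, 40% and 43%.
- If the effect grows linearly, with half of it at T1, the coefficient is (0 + 0.5 + 1)/3 = 0.50 of the T2 effect. Part of this comes from averaging T1 with T2, which alone gives 0.75. Including T0 takes it from 0.75 to 0.50.

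**5. Illustrative power.** Two-sided 5%, normal approximation, 60:30 so 1/60 + 1/30 = 0.05, d = 0.5 SD at T1 and T2, complete scores, ρ = 0.5:

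- As written: estimate 0.333, SE = √(0.05 × (1 + 2ρ)/3) = √(0.05 × 0.667) = 0.183; z = 1.826; power about 45%.
- T1–T2 mean adjusted for T0: SE = √(0.05 × [(1 + ρ)/2 − ρ²]) = √(0.05 × 0.50) = 0.158; z = 3.162; power about 88%.
- T2 alone adjusted for T0: SE = √(0.05 × [1 − ρ²]) = √(0.05 × 0.75) = 0.194; z = 2.582; power about 73%.

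At ρ = 0.3 the same formulas give 53%, 85% and 65%; at ρ = 0.7 they give 39%, 96% and 88%.

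**The case against.** The strongest reply is that the protocol calls group an independent variable, not the sole one. A longitudinal multilevel analysis often implies time and group-by-time terms, and such detail may sit in a statistical analysis plan that is not at hand. Having T0 among the outcomes is not wrong in itself either; the remedy below does the same. This stands in part: the protocol does not rule out an interaction, and if one was intended the dilution disappears. But the text does more than stay silent. It lists T0 as an outcome and names group alone as predictor, so a later plan would have to supply a different contrast, not just fill in detail. The covariate rule does not help when the groups are balanced.

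A reader might infer more than the documents support:

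- *That a third or more of the effect is lost.* One third is the complete-T0 case under a constant effect and exchangeable correlation. Because the score is for people who have returned to work and some entrants are fully sick-listed, T0 scores will probably be incomplete, and the loss smaller.
- *That the secondary questionnaire has the same fault.* Its sentence lists no visits, so this is an inference from parallel wording.
- *That the diluted estimate will set the size of the definitive trial.* Determining that size is an aim, but the protocol does not say this coefficient will be used. If it were, with an unchanged SD, a one-third shrinkage would inflate the required number by 1/0.667² = 2.25.
- *That the model plainly contradicts the stated question.* The wording is mixed: improvement is mentioned, but so is a higher score, which is a contrast of levels. A pooled average including T0 serves neither well.

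**Conclusion.** The point holds on the text as written. The named model averages the post-randomisation effect with an expected-zero T0 difference and does not estimate greater improvement. Under a constant effect and exchangeable correlation the loss is roughly 10% to 33%, depending on how many participants have a T0 score; serial correlation or a growing effect makes it larger. The share with T0 scores, the correlation and the effect pattern are all assumed. The zero T0 difference is an expectation under randomisation, not an exact value in one sample.

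The power figures assume complete scores for all 90 participants, which does not fit a measure restricted to returners. They show direction and rough size only.

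This should be corrected, but it is not critical: none of the five feasibility criteria uses the model, and effectiveness is a secondary aim with results described as preliminary.

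**What to change.** State the contrast. Use a longitudinal model for I-RTW_CS at T0, T1 and T2 with one T0 mean common to both groups, time and group-by-time terms, and RTW status at T0, which the randomisation already takes into account. Report the group difference at T2 as the effect, and show the T1 difference beside it.

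This is preferable to entering the T0 score as a covariate, because a complete-case analysis of that kind would drop returners who had no T0 score, an important group here. If QWLQ-CS is also analysed with T0 as an outcome, use the same model and list its visits.

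The change needs no new data. Its costs are slightly more modelling and, for a T2-only contrast, less power than the T1–T2 average: about 73% against 88% in the illustration above, with about 45% for the model as written. If the investigators prefer the T1–T2 average, they should say so in advance.

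### Randomisation is balanced on baseline RTW status, but the covariate rule in effect keeps that factor out of the RTW analysis; if it predicts later RTW, the unadjusted test is conservative

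*Protocol*

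**What the plan says.** Protocol, Methodology (Randomization): the "allocation ratio will be set at 2:1 (intervention vs. control group"), and allocation is "controlled the participant’s RTW status". The balancing method is not named.

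Protocol, Methodology (primary effect measure): RTW means "having performed work activities in own work or in replacement work during the past four weeks". According to the Project summary, entrants may be on full or partial sick leave, so some can already meet this definition at T0.

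Protocol, Data management and statistical analysis:
- Baseline comparability is tested: "equal distribution between the intervention and control group at baseline will be determined using chi-square tests for categorical variables", with t-tests or Mann-Whitney tests for continuous variables.
- The default analysis is unadjusted: "When no statistically significant unequal distributions will be found at baseline, the relative risk (RR) will be determined for RTW at T1 and T2". For the I-RTW_CS score, "a longitudinal multilevel analysis will be performed with the group classification as an independent variable"; no other independent variable is named.
- A covariate enters only under this condition: "significant imbalance of a prognostic factor for the primary effect measure at baseline (9, 10), this factor will be used as a covariate". RTW is then analysed by logistic regression.

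No section says that the factor used in randomisation is always part of the analysis. This is not detail left to a statistical analysis plan: the Protocol states a selection rule, and that rule decides the matter.

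**The concern.** The design singles out one variable as important enough to balance on. The analysis rule then admits variables only if they turn out unbalanced, so the variable chosen for balancing is the one least likely to be admitted.

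Balancing on a prognostic factor reduces the real sampling variation of the difference between arms. An unadjusted analysis does not see this reduction and reports the variance of an unrestricted randomisation. The confidence interval is then too wide, the test rejects too rarely under the null, and power is lost.

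This matters because Study goals and objectives ties the statement that the toolbox is effective to statistical significance on both components of successful RTW. A conservative test on the RTW component makes that statement harder to reach for a reason unrelated to the toolbox.

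**Working it through.** **Inputs from the Protocol.** N = 90 ("the sample size number of 90 participants is included within the recruitment period of six months"); 2:1 allocation, hence 60 and 30; balancing on RTW status; unadjusted RR by default. The Protocol gives no event rate, effect size, alpha or power, so there is no figure of its own to reproduce.

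**Assumptions, not in the Protocol.** Balancing works like stratified allocation. Half of the participants work at T0 (varied below). All 90 are analysed. RTW risk at follow-up is p0 in those not working at T0 and p1 in those working, varied from weak to strong prognosis.

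**Step 1: does the rule ever admit the factor?** With permuted blocks of 6 within T0 RTW strata, T0 RTW status was significantly imbalanced in 0 of 6,000 simulated trials in every scenario. Without stratification it was imbalanced in about 5%.

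**Step 2: the size by formula.** Under the null with half working at T0, the crude test uses V_crude = p(1 − p), where p = (p0 + p1)/2. The real variation under stratified allocation is V_true = [p0(1 − p0) + p1(1 − p1)]/2. The standard error is inflated by R = √(V_crude/V_true), and the one-sided error is about P(Z > 1.96R). For 40%/90%: p = 0.65; V_crude = 0.2275; V_true = (0.24 + 0.09)/2 = 0.165; R = 1.174; P(Z > 2.30) = 1.1%.

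**Step 3: simulation.** Pooled z-test (crude) against Cochran-Mantel-Haenszel (stratified), nominal one-sided 2.5%. Power is for a gain of 20 percentage points in those not working at T0 and none in the others.

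| p0 / p1 | V_crude | V_true | R | Error, formula | Error, simulated crude | Power crude | Power stratified |
|---|---|---|---|---|---|---|---|
| 60% / 70% | 0.2275 | 0.2250 | 1.006 | 2.4% | 2.6% | 16.8% | 16.9% |
| 50% / 80% | 0.2275 | 0.2050 | 1.053 | 1.9% | 2.1% | 16.2% | 17.1% |
| 60% / 90% | 0.1875 | 0.1650 | 1.066 | 1.8% | 1.9% | 21.7% | 22.5% |
| 40% / 90% | 0.2275 | 0.1650 | 1.174 | 1.1% | 1.1% | 14.0% | 18.9% |
| 40% / 95% | 0.2194 | 0.1438 | 1.235 | 0.8% | 0.7% | 14.1% | 21.4% |

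The stratified test has an error of about 2.5% throughout. At 40%/95%, with 30% working at T0, the crude error is 1.2% and power is 23.7% crude against 29.5% stratified. With 60% working, the figures are 0.7%, 10.3% and 17.0%.

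**Step 4: the planned statistic itself.** Unadjusted log RR against the Mantel-Haenszel RR, two-sided 5%, half working at T0. Power is for a conditional odds ratio of 3 in both strata.

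| p0 / p1 | Mean SE, unadjusted | True SD | Type I error, unadjusted → MH | Power, unadjusted → MH |
|---|---|---|---|---|
| 0.6 / 0.7 | 0.166 | 0.166 | 4.8% → 4.9% | 45.0% → 44.5% |
| 0.5 / 0.8 | 0.166 | 0.162 | 4.1% → 5.2% | 39.9% → 42.0% |
| 0.4 / 0.9 | 0.167 | 0.145 | 2.3% → 4.6% | 29.3% → 36.6% |
| 0.5 / 0.95 | 0.139 | 0.122 | 2.4% → 4.6% | 23.7% → 29.3% |

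Without stratification at 0.4/0.9, the mean SE is 0.167 and the true SD 0.169. The excess therefore comes from balancing on the factor and then ignoring it.

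**Step 5: the logistic branch.** At 0.4/0.9 and odds ratio 3, adjusting for T0 RTW status moves the log odds ratio from 0.867 to 1.099 and its SE from 0.507 to 0.585, so z goes from 1.71 to 1.88. The SE rises because the odds ratio is non-collapsible. Under the null the unadjusted SE is still too wide (0.476 against a true SD of 0.417).

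**The case against.** Four objections deserve an answer.

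- **The size depends on an unknown.** A reader might infer that T0 RTW status is the strongest predictor of RTW and that the standard errors are too wide in any case. The Protocol does not rank predictors; it only cites two reviews for prognostic factors. With weak prognosis (60%/70%) nothing is lost, and at 50%/80% little is. This stands: the claim has to be conditional.
- **Other outcomes.** A reader might extend the point to unwanted work changes, the I-RTW_CS score and the QWLQ-CS score. Nothing was computed for these, and the Protocol does not say that T0 RTW status predicts them. This stands too.
- **Adjustment is not free of practical limits.** At 95% RTW, a stratum of 45 has no non-event with probability 0.95^45 ≈ 10%, and its 15 controls have none with probability 0.95^15 ≈ 46%. A nearly saturated stratum adds little information, and a logistic coefficient for T0 status may not be estimable. This argues for the Mantel-Haenszel RR as the default, not for leaving the factor out.
- **The consequence is limited.** The primary aim is feasibility, and none of the five feasibility criteria uses this analysis. The effect results are called preliminary. Even after the fix, power in the strong-prognosis setting is about 21% for a 20-point gain. All true, but the Protocol still attaches its effectiveness statement to significance.

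**Conclusion.** The mismatch between design and analysis rule is in the text and does not depend on assumed rates: as written, the balancing factor is in effect never in the RTW analysis. This takes the word controlled in the randomisation paragraph to mean stratification or a similar balancing method.

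The statistical cost is conditional on how well T0 RTW status predicts later RTW. It ranges from nil (60%/70%) through small to 5 to 7 points of power with a crude one-sided error of about 0.7% to 1.1% (40% against 90% to 95%). The middle setting (50%/80%) depends somewhat on the assumed effect: under one point for a gain confined to those not working at T0, about two points for an odds ratio of 3 in both strata.

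The error is conservative. A reader might infer biased relative risks or excess false positives; neither follows. The point concerns interval width and power for the RTW component only, and it leaves the feasibility conclusions untouched. It is worth correcting mainly because the correction is so cheap.

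**What to change.** Add one sentence to Data management and statistical analysis: the between-arm analysis of RTW at T1 and T2 always stratifies by or adjusts for T0 RTW status, whatever the baseline tests show. Use a Mantel-Haenszel RR or a regression-based adjusted RR. If the logistic branch is kept, T0 RTW status is always included there as well; describe the gain as a valid test and better power, not as a smaller standard error of the log odds ratio.

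Including the same factor in the models for I-RTW_CS, QWLQ-CS and unwanted work changes is optional, for consistency with the randomisation; no gain has been shown for them.

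Cost: one sentence. The variable is already collected before randomisation. In the weak-prognosis case the stratified analysis cost about half a point of power (45.0% to 44.5%).
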